**Methods/Design:**

One hundred and fifty people with end-stage arthritis on the waiting list for total hip or knee arthroplasty will be recruited and randomly allocated to one of two groups using computer-generated block randomisation. A randomised controlled trial adhering to CONSORT guidelines will evaluate the efficacy of a mindfulness training program (weekly group-based classes in mindfulness practice, 2 ½ hours, for 8 weeks plus a 7-hour Saturday session in Week 6) prior to total joint arthroplasty, compared to a “standard care” group who will undergo routine total joint arthroplasty. Primary outcomes will be evaluated by a blinded examiner at baseline, 3 and 12 months post-surgery, using a validated self-reported pain and physical function scale. Secondary outcomes will include i) a range of validated measures of psychological wellbeing and ii) health economic analysis. All analyses will be conducted on an intention to treat basis using linear regression models. Health economic modelling will be applied to estimate the potential cost-effectiveness of mindfulness training and total joint arthroplasty.

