### Timelines

This is a 3-year study commencing June 2012 and ending May 2015. See Table 1 and Figure 1 for time points and recruitment progress.

**Table 1 T1:** Trial study visits

**Documentation**	**Visit 1**	**Visit 2**	**Visits 3–11**	**Visit 12**	**Visit 13**	**Visit 14**
Baseline data, demographics	X					
Eligibility criteria	X					
Randomisation	X					
Baseline assessments*		X				
8-week MT program+			X			
Total joint arthroplasty				X		
3 month MT booster session+					X	
3 month assessments*					X	
12 month assessments*						X

*Assessments are given to patients at their surgical review visit but completed independently. Assessments include: WOMAC; SF-12; WHOQOL-BREF; HADS; Arthritis Self-Efficacy Scale; MAAS, Carver Brief COPE; Brief Illness Perceptions Questionnaire; MMSE (administered at baseline during the pre-admission assessment).

+Applies to Attendance for Intervention Group Only.

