### Sample size

The sample size calculation was based on the following parameters: i) alpha value = 0.05, 2-sided; ii) power = 80%; iii) expected rates of the primary outcome 1-year post-TJA. To determine the sample size, we reviewed the data from our SVHM joint registry from 2009 to 2010 [44]. Of 1,180 patients who underwent TJA, 40% showed moderate to severe pre-operative psychological distress according to the pre-operative SF-12 MCS score. The mean difference in functional outcome scores at 12 months post-TJA between individuals with moderate to severe pre-operative psychological distress and individuals with no or mild psychological distress was 10 (+20) points. Based on these data, the sample size required in each of the 2 groups is 64. To allow for 15% attrition, 150 patients will be recruited in total. These numbers will also give more than 80% power to detect the expected minimum clinically important difference in pain and functional outcome scores between the combined MT + TJA group and the TJA alone group.

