### Statistical analysis

Statistical analysis will be by intention to treat. Categorical variables will be analysed using χ^2^ tests (or Fisher’s Exact test for small samples) while for continuous variables we will employ (parametric) *t*-tests and (non-parametric) Mann-Whitney tests for symmetrically and asymmetrically distributed data, respectively. The significance of differences in dichotomous data will be tested using generalised estimating equations or linear mixed model. If there are chance imbalances in baseline patient characteristics hypothesised to influence the main outcomes, then statistical techniques that allow adjustment for confounding variables will be used as secondary analyses. If there are more than 5% missing data, sensitivity analyses allowing for different assumptions, such as the best or worst possible scenario, will also be reported for the main outcomes of the study.

Health economic modelling will be applied to estimate the potential cost-effectiveness of MT + TJA. Decision analysis [46] will be used to compare the downstream consequences of MT + TJA versus TJA alone. The incorporation of Markov [47] and life-tabling [48] techniques will allow for the modelling of outcomes beyond one year. The main output of interest in health economic modelling is incremental cost-effectiveness ratios in terms of net costs per unit of health gain. Net costs will comprise the costs of MT + TJA minus costs saved from the reduction in downstream health services utilization. Health gains will be measured by estimating years of life gained and quality-adjusted life years gained. Both are enabled by the collection of time-to-outcome data and the latter also by collection of QoL data. All health economic analyses will be undertaken in accordance with recommended approaches, such as 5% discounting of estimated future costs and health gains. To account for any uncertainty in the data inputs for health economic modelling, sensitivity and uncertainty analyses will be undertaken via Monte Carlo simulation [49].

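### At the planned 15% attrition the one missing-data scenario named is too wide to test a 10-point effect, and randomised patients who never have surgery have no defined primary outcome time

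*Protocol article*

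**What the plan says.** All references are to the protocol article.

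- **Analysis principle.** The Statistical analysis section says: "Statistical analysis will be by intention to treat". The abstract says the same and names linear regression.
- **Tests.** The Statistical analysis section assigns continuous variables to t-tests or Mann-Whitney tests, depending on symmetry. Generalised estimating equations and the linear mixed model are mentioned there only for dichotomous data. Covariate adjustment is a secondary analysis, used if baseline characteristics are imbalanced.
- **Missing data.** The same section says: "If there are more than 5% missing data, sensitivity analyses allowing for different assumptions, such as the best or worst possible scenario". These analyses are to be reported in addition, for the main outcomes.
- **Expected loss.** The Sample size section says: "To allow for 15% attrition, 150 patients will be recruited in total".
- **Outcome and timing.** The primary outcome is WOMAC pain and physical function, each on a 0-100 scale. The abstract times it at baseline and at 3 and 12 months after surgery. Experimental design compares the arms at 12 months after arthroplasty.
- **Delivery.** The footnote to Table 1 (Timelines) says: "Assessments are given to patients at their surgical review visit but completed independently". Table 1 puts randomisation at Visit 1 and surgery at Visit 12.

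**The concern.** The plan expects three times the missing data that triggers its sensitivity analysis, so that analysis is likely to be needed. Best/worst case has a natural meaning for a binary outcome. On a 0-100 score, its plainest meaning is to give every missing patient a score at one end of the scale, which few real patients have. If the resulting band covers both harm and a very large benefit, it cannot tell a fragile result from a sound one.

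This matters because loss could differ by arm: only the intervention arm is asked to attend eight weekly classes and a full-day session. The travel help and reminders described under Recruitment apply to both arms and may limit this, but they do not remove it.

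The second part concerns who can have a primary outcome at all. The outcome clock starts at surgery, which comes after randomisation. A comparison that can be defined only for operated patients conditions on an event after randomisation, which is what intention to treat is meant to avoid.

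**Working it through.** **Inputs.** Sample size section: "alpha value = 0.05, 2-sided"; power 80%; "individuals with no or mild psychological distress was 10 (+20) points", with the bracket read as SD 20 (an assumption: a lost plus-minus sign); "the sample size required in each of the 2 groups is 64"; attrition 15%; total 150. Scale range 0-100 is from the Primary outcome section. Allocation of 1:1 (75 per arm) is assumed from the equal group sizes.

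**1. The plan's own figure.** n per arm = 2 × (1.96 + 0.842)² × 20² / 10² = 62.8, so 63. The exact t-test gives 63.8, so 64, with power 80.1% at 64. Attrition: 128 / 0.85 = 150.6, against 150 stated. The figure reproduces. In reverse, 150 × 0.85 = 127.5, about 2 × 64, so power was planned on patients with an observed outcome.

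**2. Precision with 64 per arm observed.** SE = 20 × √(2/64) = 3.54; 95% half-width = 1.96 × 3.54 = 6.9 points.

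**3. Scale-extreme best/worst case.** Let d be the completer difference (benefit positive) and m the share missing in each arm. Each arm's filled mean is (1 - m) × completer mean + m × assigned score. With one arm's missing scores at 0 and the other's at 100, the difference is (1 - m)d ± 100m.

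| m | d | Worst | Best | Shift from d |
|---|---|---|---|---|
| 5% | 10 | 4.5 | 14.5 | -5.5 / +4.5 |
| 10% | 10 | -1.0 | 19.0 | -11.0 / +9.0 |
| 15% | 0 | -15.0 | 15.0 | -15.0 / +15.0 |
| 15% | 10 | -6.5 | 23.5 | -16.5 / +13.5 |

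At 15% the band is 30 points wide, three times the design difference, and the sign can change.

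**4. With sampling error.** Take 11 of 75 missing per arm, d = 10, completer SD 20, and completer means of 30 (control) and 20 (intervention) with lower better; the means are illustrative. The worst case is -6.1 (95% CI -15.2 to 2.9) and the best case 23.2 (14.9 to 31.5). Control means of 40 or 50 give similar intervals.

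**5. Milder readings, m = 15%, d = 10.**
- Same extreme in both arms: 0.85 × 10 = 8.5.
- Missing scores displaced by 1 SD (20 points) in opposite directions: 10 ± 0.15 × 40 = 4 to 16.
- Displaced by 0.5 SD: 10 ± 0.15 × 20 = 7 to 13.

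**6. What a delta-adjusted analysis would show.** If missing patients' scores are displaced by a total of D points between arms, to the intervention's disadvantage, the estimate is 10 - 0.15D. Holding the half-width at 6.93, the lower limit reaches zero at D = (10 - 6.93) / 0.15 = 20.5. The estimate itself reaches zero only at D = 10 / 0.15 = 66.7. A reader can judge whether such displacements are plausible; the -6.5 to +23.5 band does not allow that.

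**7. Timing, side by side.** Randomisation is at Visit 1. Surgery is at Visit 12. Both follow-up assessments are counted from surgery and handed out at surgical review. No other origin for the outcome clock is given. For a patient randomised but never operated on, 12 months after surgery does not exist.

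**The case against.** The case against is substantial, and much of it stands.

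- A reader might infer that the plan commits to a complete-case analysis. It does not say so. The named tests use observed scores unless values are imputed, but no primary missing-data method is stated, and an article may leave that to a fuller document. Its absence is not the point here.
- A reader might take best/worst case as the whole sensitivity plan. The wording offers it as an example among different assumptions, so a delta-adjusted analysis is already permitted. What remains is that the only scenario named is the uninformative one.
- A reader might say that missing data move the result by 15 points either way. That is exact only when the completer difference is zero, with equal loss in both arms and opposite extremes. The plan does not define best and worst, and step 5 shows much narrower bands. At the 5% trigger even the extreme reading does not change the sign of a 10-point difference.
- A reader might conclude that unoperated patients are dropped, or that anyone whose surgery is deferred is lost. The documents support neither. They are silent on cancellations, and a deferred patient who is later operated on still has the review visits listed under Standard of care. Deferral moves the clock; only cancellation, or deferral past the end of the study, removes the time point.
- The documents give no interval from randomisation to surgery and no cancellation rate, so the second part cannot be sized.

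None of this answers two facts. The named tests make no use of the baseline and 3-month WOMAC scores already collected. (The abstract's linear regression could include baseline, but the article does not say that it will.) And the outcome clock has no origin for a patient without surgery.

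**Conclusion.** The point holds in limited form. At the planned 15% attrition, scale-extreme best/worst case turns a 10-point completer difference into -6.5 to +23.5, against a completer 95% half-width of about 7. It cannot test the robustness of the effect for which the trial is sized. This rests on equal attrition by arm, on all attrition becoming missing primary outcomes, and on the opposite-extremes reading.

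Separately, timing every follow-up from surgery leaves a randomised patient who never has surgery without a defined primary outcome time, which is hard to square with intention to treat. How many patients this affects cannot be estimated from the documents.

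The documents do not show that the primary analysis will be biased or that any patient will be excluded. This is a change that should be made, and it is cheap.

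**What to change.** 1. **Primary analysis.** Analyse WOMAC pain and function with a linear mixed model on the 3- and 12-month scores, adjusted for baseline, taking the arm difference at 12 months as the estimate. Alternatively, use multiple imputation from baseline and 3-month scores. A model with baseline only as a covariate still omits patients with no follow-up score; to keep them, treat baseline as one of the responses or use the imputation route. Both approaches assume that missingness is explained by the observed data, hence the next item.
2. **Sensitivity analysis.** Make a delta-adjusted (tipping-point) analysis the main one, in place of scale-extreme best/worst case. Worsen imputed scores in steps, separately by arm, until the conclusion changes. On the planning figures the range needs to pass about 20 points between arms (step 6).
3. **Cancelled surgery.** Send the same questionnaires to randomised patients whose surgery is cancelled, at a pre-specified time since randomisation, and keep these patients in the analysis.

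The cost is slightly more analysis work, a few mailings, and approximate assessment timing for unoperated patients. Treatment, recruitment and the questionnaire set do not change.

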Keeping in mind the absence of previously established psychological interventions in arthroplasty, we propose that MT prior to TJA is likely to be a particularly suitable and effective intervention, leading to better outcomes. The primary aim of this research is to determine if psychological well-being and physical recovery are improved in TJA patients if surgery is preceded by a mental health enhancement program. Two exploratory aims of this study will be: i) to compare the cost effectiveness of this combination versus standard of care; ii) to investigate the influence of mindfulness training on candidate mediators of health outcomes drawn from psychological research on adaptation to illness–notably cognitive distortions, illness beliefs, and coping styles.

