## Methods

### Experimental design

A randomised controlled trial of individuals undergoing TJA for end-stage arthritis. Patients in the intervention arm will undergo mindfulness training prior to TJA. Patients in the control arm will undergo TJA only. Outcomes will be compared at 12 months after TJA. The study strategy will be registered, constructed, and presented according to the recommendations of the CONSORT statement [26].

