### Outcome assessments

#### Data capture

Outcomes will be captured by the research associate. Demographic information collected at baseline will include age, gender, co-morbidities, body mass index, and socioeconomic data. We will also collect ‘time’ on the waiting list. All MT sessions will be audio-taped and a random sample will be selected and assessed for adherence to the principles of MT. Fully-itemised costs of healthcare will be captured via SVHM’s hospital network, including administered medications as well as costs of hospital in-patient and out-patient encounters. While beyond the scope of the initial Discovery Project time frame, the investigators will include a longer term follow-up plan in the ethics application to allow scope for continued data capture in the study group at the annual outpatient review to 10 years.

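### The net-cost definition keeps the full cost of surgery in the numerator, which does not fit the incremental comparison with surgery alone in the same paragraph

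*Protocol article*

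**What the plan says.** All references are to the protocol article.

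- **Aim.** The last paragraph of Background gives two exploratory aims. The first is "to compare the cost effectiveness of this combination versus standard of care".
- **Arms.** Under Experimental design, intervention patients have mindfulness training before surgery. For the others: "Patients in the control arm will undergo TJA only".
- **Comparison.** Under Statistical analysis, decision analysis "will be used to compare the downstream consequences of MT + TJA versus TJA alone".
- **Output.** "The main output of interest in health economic modelling is incremental cost-effectiveness ratios in terms of net costs per unit of health gain".
- **Numerator.** "Net costs will comprise the costs of MT + TJA minus costs saved from the reduction in downstream health services utilization".
- **Denominator.** "Health gains will be measured by estimating years of life gained and quality-adjusted life years gained".
- **Cost data.** Under Data capture: "Fully-itemised costs of healthcare will be captured via SVHM’s hospital network". The health services item under Secondary outcomes repeats this for in-patient and out-patient care.

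The article gives no unit cost for the course or the operation, no expected saving and no expected QALY gain.

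**The concern.** An incremental cost is the difference in total cost between two strategies. Here both strategies contain the operation, so a cost common to both should cancel. The stated numerator adds the cost of the course and the cost of the operation, and then takes off only savings in later service use. Those savings cannot stand in for the comparator's operation, which is the index procedure in both arms and is not avoided in either.

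As worded, the sentence would be a correct increment only against a comparator with no up-front cost, that is, against no surgery. The trial has no such arm.

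The stake is the main economic output. An analyst who applied the sentence as written would charge the course with the cost of an operation that controls also receive. The resulting ratio could not be read as the cost per QALY of adding MT to TJA.

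**Working it through.** There is no economic figure in the article to reproduce, so the check is algebraic.

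**Symbols, per patient**
- M: cost of MT, including the booster (Intervention section)
- T1, T0: cost of TJA in the MT + TJA arm and in the TJA-alone arm (both arms have surgery, Experimental design)
- D1, D0: downstream care cost in the two arms; S = D0 − D1 is the downstream saving
- Q: between-arm health gain, taken as positive

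**Step 1, numerator as worded:** M + T1 − S.

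**Step 2, numerator for the stated comparison:** (M + T1 + D1) − (T0 + D0) = M + (T1 − T0) − S. If TJA costs the same in both arms, this is M − S.

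**Step 3, difference:** (M + T1 − S) − (M + T1 − T0 − S) = T0. The ratio is too high by T0/Q, whatever MT costs or saves. This step does not need T1 = T0.

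**Step 4, sign:** with T1 = T0 = T, the correct numerator is negative when S > M, while the worded numerator stays positive as long as S < M + T. So for M < S < M + T, a programme that saves money would be reported with a positive cost per QALY.

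**Illustration.** Every input here is an assumption; none comes from the article. Q = 0.05 QALY and equal TJA cost in both arms throughout.

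| M | T | S | As worded, (M + T − S)/Q | Incremental, (M − S)/Q | Excess, T/Q |
|---|---|---|---|---|---|
| 2,000 | 10,000 | 0 | 12,000/0.05 = 240,000 | 2,000/0.05 = 40,000 | 200,000 |
| 500 | 30,000 | 0 | 30,500/0.05 = 610,000 | 500/0.05 = 10,000 | 600,000 |
| 1,000 | 20,000 | 2,000 | 19,000/0.05 = 380,000 | −1,000/0.05 = −20,000 | 400,000 |

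In the first two rows the worded ratio is 240,000/40,000 = 6 and 610,000/10,000 = 61 times the incremental one. The third row shows the change of sign. The rows show how the formula behaves; they do not estimate the error in this trial.

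**The case against.** The strongest defence is context. The same paragraph names TJA alone as the comparator, calls the ratios incremental and undertakes to follow recommended methods. Even the disputed sentence speaks of savings and a reduction, which only make sense relative to a comparator. On this view, MT + TJA is just the label of the intervention arm, and its cost means its extra cost. A condensed article would also leave the full costing equations to a more detailed plan.

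Much of this stands. A reader might infer that the trial plans a non-incremental ratio that will be grossly overstated. The documents do not support that: the declared comparison is incremental, and how large the overstatement would be depends on costs and gains that the article does not give.

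Two further inferences are also too strong.
- One is that the formula has no room for higher service use in the MT arm. A saving can be negative, and the planned capture of itemised costs is not limited to reductions or to one arm.
- The other is that correcting the sentence after seeing the data would open a choice of analyses. The named comparator already dictates the correction.

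What the defence does not remove is the sentence itself. It is a stated definition, not an omitted detail, and no other sentence takes off the comparator's operation. The general promise to follow recommended methods does not override a specific formula. The combined framing also recurs: the Abstract and the opening of the economic paragraph speak of the cost-effectiveness of training together with surgery, without naming a comparator in that sentence.

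**Conclusion.** The point holds as an internal inconsistency. The net-cost definition does not match the comparison of MT + TJA with TJA alone set in the same paragraph. Applied literally, it raises the incremental cost-effectiveness ratio by T0/Q and can hide a cost saving. The direction follows from algebra and needs only a positive TJA cost in the control arm and a positive health gain. The size cannot be derived from the documents.

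Severity is minor to moderate. Background calls the economic aim exploratory, and the Abstract lists health economic analysis among the secondary outcomes. The WOMAC primary outcome, the sample size and the randomisation are unaffected.

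**What to change.** Replace the net-cost sentence with a definition along these lines:

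*Net cost is the mean total cost per randomised patient in the MT + TJA arm (MT course and booster, TJA admission, downstream care) minus the mean total cost per randomised patient in the TJA-alone arm (TJA admission, downstream care), taken with whatever sign it has. The incremental cost-effectiveness ratio is this difference divided by the difference in mean health gain between the same two arms.*

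If TJA costs the same in both arms, this reduces to the cost of the MT programme minus the downstream saving.

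The change costs one sentence. It needs no new patients or visits. Itemised hospital costs are already to be captured, and the cost of the MT programme is needed under the present sentence too.
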